## Abstract

**Background:**

Accelerated partial breast irradiation (APBI) is an accepted treatment option for early breast cancer. Treatment delivered on the Magnetic Resonance integrated Linear Accelerator (MRL) provides the added assurance of improved soft tissue visibility, important in the delivery of APBI. This technique can be delivered in both the supine and prone positions, however current literature suggests that prone treatment on the MRL is infeasible due to physical limitations with bore size. This study aims to investigate the feasibility of positioning patients on a custom designed prone breast board compared with supine positioning on a personalised vacuum bag. Geometric distortion, the relative position of Organs at Risk (OAR) to the tumour bed and breathing motion (intrafraction motion) will be compared between the supine and prone positions. The study will also investigate the positional impact on dosimetry, patient experience, and position preference.

**Methods:**

Up to 30 patients will be recruited over a 12-month period for participation in this Human Research Ethics Committee approved exploratory cohort study. Patients will be scanned on the magnetic resonance imaging (MRI) Simulator in both the supine and prone positions as per current standard of care for APBI simulation. Supine and prone positioning comparisons will all be assessed on de-identified MRI image pairs, acquired using appropriate software. Patient experience will be explored through completion of a short, anonymous electronic survey. Descriptive statistics will be used for reporting of results with categorical, parametric/non-parametric tests applied (data format dependent). Survey results will be interpreted by comparison of percentage frequencies across the Likert scales. Thematic content analysis will be used to interpret qualitative data from the open-ended survey questions.

**Discussion:**

The results of this study will be used to assess the feasibility of treating patients with APBI in the prone position on a custom designed board on the MRL. It may also be used to assist with identification of patients who would benefit from this position over supine without the need to perform both scans. Patient experience and technical considerations will be utilised to develop a tool to assist in this process.

*Trial registration* Australian New Zealand Clinical Trials Registry (ANZCTR): ACTRN1262400067583. Registered 28th of May 2024. https://www.anzctr.org.au/ACTRN12624000679583.aspx

## Background

Worldwide, breast cancer is now the most commonly diagnosed form of cancer in women [1]. Early breast cancer (an invasive breast cancer, contained within the breast which may, or may not have spread to the lymph nodes in the breast or axilla) is the most common presentation of breast cancer in Australia [1]. Most patients with early breast cancer receive breast conservation surgery and radiotherapy, with studies demonstrating the highest breast cancer specific survival in this group at 98.8% [2]. It has been demonstrated that the perceived burden of radiotherapy (access, cost, travel, time away from home or off work—typically 3–6 weeks) may influence the patient’s decision to access this treatment [3]. Accelerated partial breast irradiation (APBI) is a promising treatment option, minimising radiation exposure to normal tissue and reducing toxicity, without compromising cancer control [4, 5]. In addition, ABPI is more convenient for patients (5 treatments vs. conventional 15–25 treatments) allowing for scarce radiation resources to be utilised more efficiently [6].

Recurrences in early breast cancer are most likely to occur close to the position of the original tumour, APBI focusses treatment to the tumour bed with a small margin to encompass the area at highest risk of recurrence [4]. To deliver this treatment safely and accurately, it is imperative that clinicians can access state of the art imaging and treatment technology. The superior soft tissue contrast provided by Magnetic Resonance (MR) imaging when compared to standard conventional cone beam computed tomography (CBCT) provides enhanced visual acuity of both the target and adjacent healthy tissue [7]. The integrated MR Linear Accelerator (MRL) facilitates daily plan adaption to account for variations in anatomy or positioning, as well as granting real time positional information during treatment delivery, ensuring dose is delivered to the intended target.

The effects of geometric distortion, patient, and breathing motion as well as physical limitations of the bore size and field of view are known in breast MR imaging. These translate with additional considerations to treatments using the integrated MRL [8]. Numerous studies have considered supine versus prone positions in different cohorts of patients for the delivery of whole breast [9, 10] and APBI [11]. They have suggested that a number of patients (mainly those with larger, pendulous breasts) would benefit from treatment in the prone position citing lower doses to Organs at Risk (OAR), particularly the ipsilateral lung [12]. The positional change in relative anatomy between supine and prone supports the decrease in lung dose and improved dosimetry as the position moves the target (tumour bed) away from the chest wall, avoiding lateral breast fall as can be seen in Fig. 1. Some studies have cited slightly higher heart doses in the prone position for whole breast radiotherapy, but this is not consistent across the literature and may be more dependent on the location of the tumour in the context of APBI [9, 10].

**Fig. 1 Fig1:**
[figure not shown]
Visualisation of change in position of anatomy on T1 MR Simulation images

Few studies have considered the comparison of positions for individual patients for MRL APBI treatment, with some groups suggesting that prone treatment is not feasible on this machine [8]. Until recently, commercially available prone breast immobilisation devices were neither MR safe nor practical for the limited space in the bore. Our team, therefore, worked with an industry partner (CDR Systems Inc., Calgary, Canada) to develop a MR safe solution. Therefore, we plan to assess whether the purpose-built prone board will provide a solution to support the treatment of APBI patients on the MRL and thoroughly explore the considerations of delivering this type of adaptive treatment in a magnetic environment.

## Methods/design

### Aims

The primary aim of this study is to investigate the benefits and limitations of supine and prone treatment positions for APBI planned for the MRL. This will involve a comparison of the location of the tumour bed and its proximity to OAR in each position, an assessment of the difference in geometric image distortion close to the target, and measurement of the of the patient’s breathing motion.

We hypothesise that prone positioning for APBI will result in less geometric distortion and less breathing (intrafraction) motion when compared to supine positioning. It will also increase the relative distance between the target volume and organs at risk (heart, lung(s), and chest wall) resulting in lower doses to these structures.

Primary outcomes:Quantification of geometric image distortion on planning MRI scans in both the supine and prone positions to determine whether there is a position specific difference.Measurement of relative distance from the Planning Target Volume (PTV) to the OAR in the supine and prone positions.Assessment of breathing motion for each patient in each position to determine whether motion is larger in the supine or prone position.

Secondary aims of this study include:To assess the differences in dose to the target, organs at risk and normal tissue for each patient between the supine and prone positions on planning MRI scans (simple synthetic computed tomography scans (CTs) generated from anatomical contours with bulk density overrides).To explore the patient experience of having an MRI simulation scan and whether there is a preference for the supine or prone position.

Secondary outcomes:Assess differences in dosimetry (dose in Gray) to the target, OAR and normal tissue for each patient between the supine and prone positions on synthetic CTs generated from the MRI scans.Analyse survey responses (content analysis) to ascertain whether there is a patient preference for the supine or prone position.

### Study design

This is a prospective, exploratory single-centre pilot study of patients undergoing APBI for early-breast cancer. Patients meeting the American Society for Radiation Oncology (ASTRO) favourable and certain cautionary criteria for APBI will be invited to participate (Table 1) Patients with known contraindications to radiotherapy such as ataxia telangiectasia and systemic sclerosis will be excluded [13]. Participants will be asked to provide written informed consent. Participation will not alter the management of the patients but will inform the decision-making process for the choice of treatment position for future patients treated with ABPI, based on the study outcomes.

**Table 1 Tab1:** ASTRO APBI Favourable and cautionary suitability criteria [13]

Features	
Age	≥ 50 years
Subtype	IDC and DCIS
Size	≤ 3cm
Grade	< 3 (1 or 2)
Margin	Negative ≥ 2 mm
Lymphovascular space invasion	Absent
Hormone (ER) Positivity	Yes
Her2	Negative
Nodal Status	Negative or pN_ITC_

Participants will be scanned on a dedicated Philips Ingenia Ambition MR-RT 1.5T MRI simulator (Koninlijke Philips N.V., Amsterdam, Netherlands) in both the supine and prone positions for APBI as per current departmental standard of care. Assessment of positioning, geometric distortion, patient and breathing motion, and dosimetry will be completed using the de-identified data from these scans. In addition, immediately following the MRI simulation session, participants will be invited to complete a short anonymous electronic survey (using closed and open-ended questions) about their experience of the planning MRI scans (MR specific sensations, information provided about the procedure and positional preferences). CT simulation and treatment will be completed as per standard protocol with appropriate immobilisation equipment in the preferred position (supine or prone as a clinical decision after MR image review) with no further study-based requirements.

### Recruitment

Participants will be invited to participate and provided with the relevant study information to make an informed decision about their participation by their Radiation Oncologist (RO) in their initial consultation if they are eligible for treatment with APBI and meet the study inclusion criteria.

### Positioning assessment

Participants will attend for MRI simulation prior to CT simulation in alignment with standard departmental protocol. For the supine MRI scan, patients will be positioned with both arms up supported by a custom vacuum bag. For the prone MRI scan, patients will be positioned on the Low Procline™ (CDR Systems Inc. Calgary, Canada), which was developed in collaboration with one of our investigators. To make the positional, distortion and breathing motion assessment the standard breast MRI sequences (T1, T2 and Cine imaging) will be acquired in each position, optimised for each laterality. The minimum distance will be calculated between the Target volume and heart, lung(s), skin rind (5mm inside the patient contour), and chest wall.

Participants will be assigned to have either the supine or prone MRI scan first (alternating between the positions) as they are recruited, to reduce bias towards the first or second scan. The order will also be recorded and considered in the analysis of results.

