#### Patient experience

Quantitative survey results will be interpreted by comparison of percentage frequencies across the Likert scales. Chi Squared and Fishers Exact tests may be used to test for differences between categories, with McNemar’s test used to compare paired responses between prone and supine positioning.

Qualitative data from the open-ended survey questions will be analysed using thematic content analysis [16].

Data will be collected in a Research Electronic Data Capture (REDCap) database and/or Microsoft Excel with statistical analysis planned to be conducted using Stata version 18.0 (StataCorp, College Station, Texas, USA), with a *p*-value of < 0.05 used to indicate statistical significance.

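### Scan order is set by predictable alternation where a concealed random list would cost almost nothing; the paired supine-prone comparison is largely protected, so this is a minor improvement

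*Protocol article*

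**What the plan says.** The Positioning assessment section of the protocol article sets the rule: "Participants will be assigned to have either the supine or prone MRI scan first (alternating between the positions) as they are recruited, to reduce bias". The bias it aims at is named in the same sentence ("to reduce bias towards the first or second scan"), and the next sentence adds: "The order will also be recorded and considered in the analysis of results". The article does not say who keeps the sequence or when a patient's order becomes known to staff.

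Four other places bear on the point:

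- Study design: "This is a prospective, exploratory single-centre pilot study of patients undergoing APBI for early-breast cancer". There is therefore one running sequence. All participants are scanned in both positions as standard care.
- Recruitment: patients are "provided with the relevant study information to make an informed decision about their participation by their Radiation Oncologist (RO) in their initial consultation", so the person inviting them has met them.
- Statistical analysis: the supine-prone tests are paired.
- Discussion: BMI, breast size, tumour bed size and tumour location are to inform a later process for choosing position without two scans.

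**The concern.** Alternation equalises the number of patients per order. It does not make the two order groups comparable, because nothing in it is random. After the first patient, each order follows from the one before. A recruiter or scanner team that knows the last order could, even without intending to, influence which of two neighbouring patients goes prone first, for instance by build or expected difficulty lying prone.

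Two kinds of result could suffer:

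- **Between-patient analyses.** Considering order means comparing prone-first with supine-first patients, and pairing does not protect that comparison. The same holds for asking which patient types do better in which position.
- **The paired difference itself**, if the order effect differs by patient type, for example if tiring by the second scan is worse in larger patients. Breathing motion and the comfort and ease ratings could plausibly change between a first and a second scan.

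**Working it through.** The plan gives no figure for order effects, power or error rates, and its sample size is pragmatic, so there is no stated figure to reproduce. The check asks which quantities predictable order can bias, and by how much under stated assumptions.

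**Inputs from the article:** alternation, one centre, both scans in every participant, paired tests, up to 30 prospective patients (15 per order if full).

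**Assumed inputs (not in the article):** size of the order effect, how it varies by patient type, and the share of patients steered.

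**1. Predictability of the next order**

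- Alternation: 100% once the previous order is known.
- Permuted blocks of random size 2, 4 or 6, best simple guess: 69.8%.
- Simple randomisation: 50%, but with a 9.9% chance of a 20:10 split or worse in 30 patients.

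**2. Model.** For patient i the supine-prone difference is d_i = τ_i + s_i·π_i. Here τ_i is the position effect, π_i the order effect, and s_i = +1 if prone first, −1 if supine first. All are in SD units of d.

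**3. Constant order effect.** If π_i = π for everyone, the mean of d is mean(τ) + π·mean(s). With 15:15, mean(s) = 0, so the bias is 0 whatever the steering.

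**4. Order effect that varies with breast size.** Let breast size x be standard normal and π_i = 0.5·x_i. In a fraction q of adjacent pairs the larger-breasted patient goes prone first. The expected larger of two standard normal values is 1/√π = 0.564 (here π is the circle constant), so mean(s·x) = 0.564q and the bias is 0.5 × 0.564 × q:

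| q | Bias of position estimate |
|---|---|
| 0 | 0 |
| 0.25 | 0.07 SD |
| 0.5 | 0.14 SD |
| 1 | 0.28 SD |

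For scale, the standard error of a 30-patient paired mean is 1/√30 = 0.18 SD. Under the same interaction, a properly randomised order would still leave a chance error of about 0.5/√30 = 0.09 SD.

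**5. Two-type version.** Take 15 patients of type A and 15 of type B, with a share p of type A and 1 − p of type B scanned prone first.

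- Overall position bias = (2p − 1)(π_A − π_B)/2. With π_A = 0.8 and π_B = 0.2 this is 0.12, 0.18 and 0.30 at p = 0.7, 0.8 and 1.0.
- Unadjusted type-by-position contrast, constant order effect 0.5: bias = 2 × 0.5 × (2p − 1) = 0.4, 0.6 and 1.0.
- Estimated order effect when the position effect differs by 0.5 between types: 0.5 + 0.5(2p − 1)/2 = 0.60, 0.65 and 0.75, against a true 0.50.
- At p = 0.5 (no steering) every bias is 0.

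**6. Which outcomes have a route to an order effect.** Distortion is read from a phantom grid, target-to-organ distance from anatomy, and dose from a plan. None has an evident dependence on which scan came first. Breathing motion and the survey do.

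**The case against.** A reader might infer that alternation biases the supine-prone comparison generally, or that staff know the order and will steer it. The documents support neither. Each patient is her own control, so steering cannot create a patient-mix difference between positions. Near-equal counts per order, which alternation delivers, are enough to cancel a constant order effect, and order is recorded as well. That staff know the next order is an inference from the absence of any described concealment.

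Steering would also be awkward and poorly motivated. Order is assigned as patients are recruited, and 30 patients in 12 months is about one every 12 days (365/30), so swapping neighbours would usually mean delaying one of them. Both scans are done in any case.

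It is also tempting to quote the inflated false-positive rate for a prone-first versus supine-first test: 12-19% instead of 5% at 50% steering, if breast size correlates 0.5-0.7 with the supine-prone difference. That is illustrative only. The order contrast is not a listed outcome, and the correlation is assumed. The Background links larger breasts to lower organ dose when prone, not to breathing motion or comfort.

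Most of this objection stands, and it limits the point to a minor one. It does not remove it: alternation is deterministic, and adjusting for order cannot separate order from patient type where the two coincide.

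**Conclusion.** The point holds in limited form. Scan order is foreseeable under the stated rule and could become linked to patient type. The overall supine-prone comparison is unbiased under a constant order effect with balanced orders. Distortion, target-to-organ distance and planned dose have no evident exposure in their overall comparison.

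The exposure is confined to two places:

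- Breathing motion and survey ratings, if the order effect varies by patient type. The bias is about 0.14 SD under 50% steering and a 0.5 SD-per-SD interaction, which is less than one standard error at 30 patients.
- Any analysis of order itself, or of patient type by position as the Discussion intends.

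Both inputs to the 0.14 SD are assumptions, and with no steering the bias is zero. This is a minor, inexpensive improvement to an exploratory pilot, not a flaw that undermines it.

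**What to change.** In the Positioning assessment section, replace the parenthesis on alternation with wording such as: *Scan order (supine-first or prone-first) will be randomised 1:1 from a computer-generated list in permuted blocks of random size (2, 4, 6), held in REDCap and revealed only after consent, once the MRI simulation appointment is booked.* State that order is analysed as randomised.

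**Cost.** A short amendment and a list loaded into the system already named ("Data will be collected in a Research Electronic Data Capture (REDCap) database"). The sample size, the number of scans and patient management do not change.

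**Downside.** If recruitment stops mid-block the orders may differ by up to three patients, against one under alternation. For example, a 15:12 split with a constant order effect of 0.5 SD leaves 0.5 × 3/27 = 0.06 SD in the unadjusted mean, which including order in the model removes.

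**Limit.** The change does not reach the existing datasets (up to 30) described under Sample size estimation, whose scan order was not assigned by the study. Those enter the distortion, positioning and dosimetry analyses, not breathing motion or the survey.

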### Geometric distortion assessment

Geometric distortion in MRI is a known artifact arising from inherent magnetic field inhomogeneities that becomes larger further from the imaging isocentre [14]. Geometric distortion will be assessed in MIM Maestro® version 7.1 or later (MIM) utilising the dPhantom (3DOne Australia Pty Ltd, QLD, Australia), a specific MRI distortion phantom containing a 2 cm MRI visible grid. Two MR images will be taken of the phantom; a reference that is centred in the bore, and a second MR will be taken with the phantom shifted a known distance to cover the region of interest, e.g., Breast. Patient images in the supine and prone positions will be contoured, and structures transferred to the shifted MR. The shift from the ground truth 2 cm grid will be calculated within each contour. The mean and maximum shifts will then be calculated as a measure of geometric distortion for each contour to support comparison of distortion between the two positions.

### Breathing motion assessment

Cine imaging sequences in sagittal-coronal directions acquired during the MRI simulation in both the supine and prone positions will be used to assess the range of breathing (intrafraction) motion. Images will be collected for 1-min intervals at multiple timepoints within the session in each position. Imaging and treatment will be performed with the patient free breathing. Motion will be measured across a minimum of five breathing cycles using tumour or surrogate edge displacement in Anterior/Posterior, Superior/Inferior and Left/Right directions. The exhale baseline drift will be assessed across the breathing phases and the mid-point between maximum and minimum exhale position will be used as the reference point. The maximum and average extents of the motion will be measured in both the supine and prone positions for each patient.

### Dosimetric assessment

Patients will have all subsequent planning and treatment performed as per the standard departmental protocol. There is no change to usual care for radiotherapy planning procedures.

For study purposes, each patient’s supine and prone MR scans will be contoured (target volumes, appropriate OAR and structures requiring a specific electron density override) using MIM then used to make a pseudo-CT; average densities will be acquired from the collective supine and prone CT scans (acquired as part of the patient’s standard of care) and applied as average population bulk densities to structures as appropriate in the Elekta Monaco™ version 5.51.11 or later (Elekta solutions AB, Stockholm, Sweden) radiotherapy treatment planning system.

In this study protocol, a MR-only workflow will not be used. Every patient will receive a CT scan following their MR sim appointment in the treatment position which will provide patient specific electron densities as per current clinical practice in our department. Contours will be applied to the MRI and bulk electron densities will be assigned to the contours in the planning system as per the current MRL workflow to create the synthetic CT. Quality assurance of the average population electron density will be performed in line with the departmental protocol for online adaptive treatment, recalculating the treatment plan on the CT and comparing the dosimetry from the planning CT and the synthetic CT.

Target volumes will be contoured by RO study investigators and all other structures by RTs. The primary target volume will consist of visible seroma and the surrounding post operative tumour bed. Standard departmental margins will be applied to generate the Clinical Target Volume (CTV) and planning target volume (PTV). APBI plans for 30 Gray (Gy) in 5 fractions with the Elekta Unity™ (Elekta solutions AB, Stockholm, Sweden) MR Linac beam model will be completed for comparison on the pseudo-CT scans in both the supine and prone positions. Beam angles will be optimised to the ipsilateral side and adjusted appropriately for tumour location, patient position, treatment laterality and to avoid entry through the cryostat pipe. Planning considerations specific to the Unity; couch top, MR radiofrequency coil and structure/density layering will also be applied. Calculation and sequencing parameters will adhere to standard departmental protocol for APBI. Doses to the targets and OAR (Heart, Lung(s), ipsilateral chest wall, ipsilateral (breast–PTV), contralateral breast and skin rind (5mm)) will be collected to ascertain whether a particular position provides a benefit over the other dosimetrically.

